### Study Design

The design of this study corresponds to a superiority randomized controlled clinical trial, conducted in public primary care clinics, to evaluate the effect of an SFBI and compare it with usual care, consisting of brief counseling and an educational brochure. The experimental and control groups will consist of primary care patients who report intermediate- to high-risk substance use and will be randomly assigned to each group. In addition, the acceptability and relevance of the applied intervention will be explored among participants in the experimental group using a qualitative approach, which focuses on a deep understanding of experiences considering the subjectivity and meanings attributed to them by individuals [34], through focus groups and qualitative analysis of their content. This study is guided by the SPIRIT (Standard Protocol Items: Recommendations for Interventional Trials) checklist (Multimedia Appendix 1).

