### Recruitment

Since in PHC centers the Alcohol, Smoking, and Substance Involvement Screening Test (ASSIST) is applied routinely—in preventive check-ups—to individuals aged 20-65 years, the staff members responsible for applying this test at each PHC clinic will invite individuals whose scores are equal to or higher than 11 on the ASSIST for alcohol and 4 for other substances to participate in this study. If they accept, they will be given an appointment with the research coordinator or a research assistant, who will formally invite them to participate.

The inclusion criteria are as follows: participants must have an ASSIST score of 11 or higher for alcohol and a score of 4 or higher for other substances, be able to communicate verbally with others, be willing to participate in the intervention, and be willing to complete the measurement instruments.

The exclusion criteria are as follows: participants with a severe and untreated mental illness such as schizophrenia, those not willing to participate in the intervention, those not willing to complete the measurement instruments, those who have received another brief intervention within the last year, and those currently being treated in another program for substance use will not be eligible to participate.

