#### ASSIST

This 8-item questionnaire developed by the WHO, is used to detect risk in substance use [37]. It predicts low, intermediate, and high risk due to substance use. It is a relatively new instrument, recently validated in Chile and recommended by the WHO for assessing risk in alcohol and substance use. The validation in Chile [40] considers a score equal to or greater than 11 for intermediate to high-risk alcohol consumption and a score equal to or greater than 4 for intermediate to high-risk substance use. It is one of the main dependent variables of the study and will be administered at baseline and follow-ups.

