### Analysis Plan

For quantitative-specific objective 3, we will use the standard *P*<.05 criterion to make inferences. Tests to detect any potential differences between individuals who received interventions from either social workers or psychologists will be conducted. The analysis approach for each specific objective is described in the following sections.

#### Specific Objective 1

The first specific objective aims to determine whether the SFBI reduces substance use patterns and risk-level substance use of participants at the 3-month, 6-month, and 9-month follow-ups (post baseline). A descriptive analysis of the recorded variables will be conducted for each participant in the experimental group, pretreatment, and at 3 months, 6 months, and 9 months post baseline. Minimum and maximum values will be reported, and the normality of their distribution will be assessed using frequency histograms and the Shapiro-Wilk normality test. Categorical variables will be described using absolute and percentage frequencies. For individuals participating in the experimental group, the following analyses will be conducted separately at each posttreatment measurement (3 months, 6 months, and 9 months): the change in frequency and quantity of consumption according to the TOP instrument will be calculated for each participant, with the mean change and its corresponding CI estimated, and a paired repeated-measures ANOVA conducted to evaluate whether there is a significant treatment effect on the average weekly consumption; if the normality assumption is not met, the nonparametric Wilcoxon signed-rank test will be used. In addition, the percentage of individuals who decrease their risk category will be calculated, and their respective CIs estimated, and, since the TOP contains categorical items, the McNemar test will be applied to evaluate whether significant changes occurred.

#### Specific Objective 2

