The third specific objective aims to determine whether participants receiving the SFBI improve their substance use patterns, substance use risk level, consequences of substance use, and mental health symptoms as compared with those receiving a minimal intervention. A descriptive analysis of the recorded variables will be conducted for each participant in both experimental and control groups at baseline and at 3 months, 6 months, and 9 months post baseline. Quantitative variables will be described using mean, SD, median, minimum, and maximum values, and their distribution normality will be assessed using frequency histograms and the Shapiro-Wilk normality test. Categorical variables will be described using absolute and percentage frequencies. For each posttreatment measurement (3 months, 6 months, and 9 months), the following analyses will be conducted: the change in substance use patterns and substance use risk level (TOP) will be calculated for each participant in both experimental and control groups, and the mean with its corresponding CI will be estimated; the change in the PHQ-9 score will be calculated for individuals in both experimental and control groups, and the mean with its corresponding CI will be estimated; the change in the GAD-7 score will be calculated for individuals in both experimental and control groups, and the mean with its corresponding CI will be estimated. Baseline characteristics, including demographic background and sociofamilial situation, of participants in the control and experimental groups will be compared, with *t* tests or Wilcoxon-Mann-Whitney tests used for quantitative variables when the normality assumption is unmet, and the Fisher exact test used for categorical variables. Given that this is a superiority design, 1-tailed tests will be used for the following comparisons. The mean decrease in monthly consumption will be compared between individuals in the experimental and control groups using a mixed ANOVA, with group (experimental and control) as the between-subjects factor and time of measurement (pretreatment, 3 months, 6 months, and 9 months) as the within-subjects factor. Similarly, mean PHQ-9 scores will be compared between the two groups using a mixed ANOVA, with group (experimental and control) as the between-subjects factor and time of measurement (pretreatment, 3 months, 6 months, and 9 months) as the within-subjects factor, with the Friedman-aligned ranks test applied if the variable normality assumption is unmet. Finally, the percentage of individuals who decrease their substance use patterns and risk (TOP) will be compared between the experimental and control groups, using the Fisher exact test.

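### Risk level is tested between arms only as a yes/no decrease, credited to the TOP, which has no described risk category; the baseline-adjusted ASSIST score would use the same data with more power

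*Protocol article*

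**What the plan says.** - **Entry (Recruitment).** The criterion is "participants must have an ASSIST score of 11 or higher for alcohol and a score of 4 or higher for other substances". I read this as either threshold qualifying, by substance.
- **Risk classes (Instruments, ASSIST).** On the ASSIST: "It predicts low, intermediate, and high risk due to substance use". The Chilean validation "considers a score equal to or greater than 11 for intermediate to high-risk alcohol consumption", with 4 as the corresponding figure for other substances. No number is printed for the step from intermediate to high. The same section says of the ASSIST: "It is one of the main dependent variables of the study and will be administered at baseline and follow-ups".
- **TOP (Instruments).** Three sections and 17 questions on recent use, offending, and health and functioning. No risk category is described.
- **Between arms (Analysis Plan, Specific Objective 3).** "the percentage of individuals who decrease their substance use patterns and risk (TOP) will be compared between the experimental and control groups", by a Fisher exact test, among the comparisons declared one-tailed. The mixed ANOVAs cover monthly consumption and PHQ-9. The ASSIST score has no between-arm test.
- **Within the experimental arm (Specific Objective 1).** At each follow-up, "the percentage of individuals who decrease their risk category will be calculated, and their respective CIs estimated", with a McNemar test that the article justifies by the categorical items of the TOP.

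**The concern.** Risk level is named in the objectives and hypotheses, and the ASSIST is called a main dependent variable. Yet the one formal comparison of risk level between arms uses a yes/no outcome credited to an instrument with no described risk category. The natural reading is that an ASSIST category is meant.

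On that reading, participants were selected for scoring at or above the same line that separates low risk from the rest. Some will cross it at follow-up through measurement error alone. Others will already be below it when the ASSIST is repeated at baseline, and they cannot then move from at risk to low whatever treatment does. Both features, together with cutting a score into two, weaken the comparison. A real effect on risk level could be missed. In the uncontrolled Objective 1 analysis, crossings due to noise or regression to the mean could be reported as response to treatment.

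**Working it through.** **1. The plan's own figure.** The Sample Size section gives 96, then 160, then 320. For the group-by-time interaction, λ = f²·N·m/(1−ρ), with f=0.12, N=96, m=4 and ρ=0.5 (ρ is assumed; the article does not state it). So λ = 0.0144 × 96 × 4 / 0.5 = 11.06, and power is 0.8002. Then 96/0.6 = 160 and 2 × 160 = 320. The figure reproduces, but it powers the mixed ANOVA. No power is stated for the Fisher test.

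**2. Number available.** 320 × 0.6 = 192 completers, or 96 per arm if allocation is 1:1. Since evaluation is planned by substance, 96 is the favourable case.

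**3. Assumptions.** The article gives neither ASSIST reliability nor a score distribution. I assume reliability of 0.7 to 0.9, those at or above the cut-off being the top 3-20% of people screened, and normal or exponential true scores. Only moves from at risk to low are modelled, because no upper cut-off is printed.

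**4. No true change, fresh baseline ASSIST.**
- Moving from at risk to low by noise: about 8-18% of all participants.
- Already below the line at baseline: about 19-66%.

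One case in detail (normal scores, top 20%, reliability 0.7): 43.5% are below the line at baseline, 16.4% move down and 16.3% move up by follow-up.

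**5. Type I error.** Noise falls equally on two randomised arms. In exact calculations at 96 per arm, the one-sided Fisher test rejects in 0.034-0.037 of null trials, below the nominal 0.05.

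**6. Power in the same case, d=0.24.** The shift raises the percentage who decrease from 16.4% to 21.8%, a difference of 5.4 points. Exact one-sided Fisher power is 0.19.

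**7. Power of the score.** The standardised effect is 0.24 × √(96/2) = 1.663. With baseline adjustment it is divided by √(1−r²), where r is the baseline to follow-up correlation. Power is Φ(that value − 1.645).

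| r | Standardised effect | Power |
|---|---|---|
| 0 (unadjusted) | 1.663 | 0.51 |
| 0.5 | 1.663/0.866 = 1.920 | 0.61 |
| 0.7 | 1.663/0.714 = 2.329 | 0.75 |
| 0.9 | 1.663/0.436 = 3.815 | 0.98 |

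**8. Across all scenarios.** Fisher power is about 10-58%: roughly 12-47% with a fresh baseline, and higher if the screening score served as baseline. The baseline-adjusted score gives 54-99% and was ahead in every scenario.

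**The case against.** **The endpoint is labelled TOP.** As written, it is not an ASSIST endpoint, so tying it to the 11/4 line is an inference. That is true and should be stated. But the ASSIST is the only instrument described as classifying risk, and if the TOP is really meant, the article describes no category that could decrease.

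**Three levels are named.** A reader might infer that a lower category can only mean re-crossing the entry line. The article does not support this: it enrols "primary care patients who report intermediate- to high-risk substance use and will be randomly assigned to each group", so a move from high to intermediate also counts. The noise percentages above leave that step out.

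**Noise is shared by both arms.** A reader might infer that noise swamps or distorts the Fisher test. It does not: there is no between-arm bias and no excess type I error. Much of the loss comes from dichotomising and a small effect. At the 20% cut-off with the screening score as baseline, Fisher power moves only from 0.31 to 0.34 as reliability rises from 0.5 to 0.9, against 0.51 for unadjusted means. With a fresh baseline, reliability matters more (0.14 to 0.26).

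**Screening score as baseline.** A reader might infer from the missing ASSIST row in Table 1 that the screening score is the baseline. Nobody would then start at low risk, 19-65% would cross by noise, and McNemar would almost always reject. The ASSIST section and the text above Table 1 instead place the ASSIST at baseline and at follow-ups, so that scenario should not carry the argument.

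**Risk level is also summarised as a mean change.** Specific Objective 3 plans this with a CI for each arm. That is useful, but it too is credited to the TOP and is not a between-arm test.

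**The gain rests on assumptions.** At r=0.5 the adjusted score reaches only 0.61. The direction is consistent; the size is not fixed by the article.

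**Conclusion.** The point holds as one of power and definition. The only between-arm test of risk level uses a dichotomised outcome credited to an instrument with no described risk category. On the natural ASSIST reading, the one printed boundary is the entry line. At 96 completers per arm, d=0.24 and one-sided 5%, the planned test has about 10-58% power against 54-99% for the baseline-adjusted ASSIST score. Both ranges rest on assumed reliability, selection fraction and score distribution. The randomised comparison remains valid. The percentage in Objective 1 has no control arm and cannot be read as a treatment effect.

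**What to change.** **Specific Objective 3.** Make the between-arm test of risk level a comparison of the ASSIST substance score at 3, 6 and 9 months, adjusted for the ASSIST score re-administered at baseline, and correct the TOP attribution. Keep the percentage who decrease category as a descriptive figure in both arms, with the percentage who move up beside it. Do not require confirmation at a later visit: a decrease first seen at 9 months could then never count, although 9 months is a stated time point.

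**Specific Objective 1.** Base the risk-category change and the McNemar test on the re-administered baseline rather than the screening score, and state that the single-arm percentage is not a treatment effect. An ASSIST row in Table 1 would remove the doubt about which baseline is used.

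**Cost.** Wording only. The ASSIST is already planned at these visits, and the article reports that no analyses have been conducted, so the change is still prospective. The small downside is that a score difference is less intuitive than a percentage, which is why the percentages stay as description.

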### Sample Size

The necessary sample size was calculated considering the minimum effect size found in evidence-based psychosocial interventions for substance use disorders (Cohen *d*=0.24 for polysubstance use, equivalent to Cohen *f*=0.12) [35]. The calculation was performed using the G*Power (Heinrich-Heine-Universität Düsseldorf) statistical software for sample size calculation [36], considering 80% power and a significance level of 5%. For the interaction effect between within-subject and between-subject factors in mixed ANOVA (details available in the Analysis Plan section), a sample size of 96 individuals was obtained, and after considering a 40% attrition rate [24,35] in follow-up, it increases to 160 individuals. The evaluation of the SFBI will be conducted separately by substance type (evaluating its effectiveness separately for at least alcohol, cocaine, and cocaine base paste, considering possible overlaps between them and marijuana). Thus, we plan to recruit 320 participants.

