#### Data Exclusion and Missing Data

Analyses will be conducted including and excluding outliers and differences between these analyses will be reported. Analyses will be performed according to the intention-to-treat principle. Missing data will be handled using multiple imputation.

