## Results

Funding for this study started in April 2024. As of the submission date of this protocol, 9 primary care clinics from 2 regions of Chile are participating in this study; 55 practitioners (30 social workers and 25 psychologists who work in these clinics) have been trained in a 36-hour course on the theory and practice of the SFBI model. The recruitment phase for participants started in February 2025 and will continue until December 31, 2026. To date, a total of 2542 ASSIST assessments have been reported by the clinics. A total of 82 patients have been referred to the study, 73 have been enrolled, and 23 have dropped out, leaving 50 currently enrolled (32% attrition).

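### The Fisher exact test named for the between-group responder comparison fits poorly with the prescribed multiple imputation; a risk difference pooled by Rubin's rules would hold the 5% level with slightly more power

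*Protocol article*

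**What the plan says.** Three statements in the Protocol article bear on this point.

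- **Analysis Plan, Specific Objective 3.** The percentage of patients whose TOP substance use and risk decrease "will be compared between the experimental and control groups, using the Fisher exact test". The section makes the outcome comparisons one-tailed at P<.05. This is the only between-group test it names for risk level, and one of those bearing on the primary outcome.
- **Data Exclusion and Missing Data.** Analyses follow intention-to-treat, and "Missing data will be handled using multiple imputation". No exception is made for the responder comparison.
- **Sample Size.** The calculated 96 is raised for dropout: "after considering a 40% attrition rate [24,35] in follow-up, it increases to 160 individuals". Planned recruitment is 320. The Results section reports 23 dropouts among 73 enrolled, given as 32%.

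**The concern.** Multiple imputation produces several completed data sets. A patient without follow-up can be a responder in some and a non-responder in others. Rubin's rules combine an estimate and its standard error from each set, adding the between-set variation that reflects what is unknown about the missing outcomes. Fisher's test takes one 2x2 table of whole counts and returns a P value, with no standard error to feed into those rules.

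The analyst must then either combine the P values by a special method, test something else, or take a shortcut. Shortcuts that treat imputed outcomes as if observed understate the variance. With up to 40% of outcomes imputed, that choice could decide significance on the only named between-group test of risk level.

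**Working it through.** **1. The plan's own figures.** For the within-between interaction of a mixed ANOVA, λ = f²·N·m/(1−ρ). With f = 0.12, N = 96, m = 4 measurements and an assumed ρ = 0.5 (not stated; sphericity also assumed), λ = 0.0144 × 96 × 4 / 0.5 = 11.06. With 3 and 282 degrees of freedom at 5%, power is 0.800, so 96 reproduces. 96/(1 − 0.40) = 160 reproduces. 23/73 = 31.5%, which rounds to the reported 32%. At 320 recruited, 0.40 × 320 = 128 outcomes would be imputed.

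**2. Assumptions for the check (not in the protocol).** 160 per arm (320/2), 45% responders under the null, 58% versus 45% under the alternative, data missing at random, 20 imputations drawn from each arm's observed rate, one-tailed 5%.

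**3. What theory predicts.** Let W be the variance that would apply with all outcomes observed. With 40% missing, the true variance of the estimate averaged over imputations is W/0.6 = 1.667W, so the between-imputation variance is 0.667W.

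- Averaging over imputations but using W as the variance: null rejection is 1 − Φ(1.645 × √0.6) = 10.1%. At 32% missing, 1 − Φ(1.645 × √0.68) = 8.7%.
- Analysing one imputed set: the variance is 1.667W + 0.667W = 2.333W, so null rejection is 1 − Φ(1.645/√2.333) = 14.1%.
- Pooled risk difference: about 0.6 × 160 = 96 observed per arm, so SE = √[(0.58×0.42 + 0.45×0.55)/96] = 0.0715. Power is Φ(0.13/0.0715 − 1.645) = 57%.

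Fisher's discreteness should pull the first two figures down somewhat.

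**4. Simulation at 40% missing.**

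| Method | Null rejection | Power, 58% vs 45% |
|---|---|---|
| Risk difference, Rubin's rules | 5.0% | 56% |
| Fisher P values combined on the z scale | 4.0% | 52% |
| Fisher on completers only | 3.6% | 51% |
| Fisher, median P over imputed sets | 8.3% | not valid |
| Fisher on one imputed set | 12.5% | not valid |

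Other runs under the same assumptions put median P as high as 9.1% and the single set as high as 13.6%. These agree with step 3 after allowing for Fisher's conservatism.

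**5. Sensitivity.** At 32% missing, null rejection is 4.9% (pooled risk difference), 3.9% (z-combined Fisher) and 3.6% (completers), with power 60%, 56% and 55%. With 30% responders under the null and 40% missing, null rejection is 5.6%, 4.2% and 3.7%. For 30% versus 45%, power is 67.9%, 64.6% and 63.0%. The ordering does not change.

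**The case against.** The strongest reply is that nothing here is broken. Multiple imputation is precisely the rule that scores dropouts: TOP is imputed and responder status is derived in each completed set. Fisher P values can be turned into z values and combined with their between-imputation variance, and the result stays below 5%. The inflated rates belong to shortcuts the protocol never mentions, and analysing one imputed set would not be multiple imputation at all. How results are pooled is a detail commonly left to a statistical analysis plan, which is not shown. Part of Fisher's power loss is its ordinary conservatism: a mid-P version of the z-combined test gave 4.75% null rejection and 54.5% power at 40% missing.

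All of that stands, and it limits the point. A reader might infer that dropouts receive no usable score, or that the two stated rules cannot be carried out together. The documents support neither. Nor do they support saying that the trial will have an inflated error rate, because they choose no shortcut.

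What survives does not rest on an omitted detail. The article itself names the test, and that test is an awkward partner for the missing-data rule it also names. Combining on the z scale gives up exactness, the usual reason to choose Fisher, and keeps the conservatism.

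**Conclusion.** The point holds as a modest improvement. For the between-group responder comparison, a risk difference pooled by Rubin's rules fits the stated imputation directly, holds the 5% level, and gains about 4 points of power over z-combined Fisher and 5 over completers-only Fisher (56% against 52% and 51%). It also removes the temptation of shortcuts that would reject in about 8% to 13% of null trials.

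These sizes rest on 160 per arm, the assumed responder rates, data missing at random and 40% missing. The imputation used only arm and observed outcome, so the gain over completers reflects Fisher's conservatism, not information recovered from other variables. Sample Size says evaluation is separate by substance, so actual tables may be smaller; that case was not simulated.

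The point should not be stretched to the other tests. The McNemar test and the rule that "if the normality assumption is not met, the nonparametric Wilcoxon signed-rank test will be used" belong to the single-arm, pre-post analyses of Specific Objective 1. The Friedman-aligned ranks fallback in Specific Objective 3 is attached to the PHQ-9 comparison.

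**What to change.** In Specific Objective 3, replace the Fisher exact test for the share of patients who decrease with a risk difference by arm (or a logistic regression with arm as a term), estimated in each imputed data set and pooled by Rubin's rules. Keep Fisher for the baseline tables, or as a sensitivity analysis labelled completers-only.

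The cost is a sentence of analysis-plan wording and a little programming. The article reports that no analyses have been done, so the change can still be made in advance. The one drawback is that the P value becomes approximate instead of exact, which is also true of z-combined Fisher. Treatment and data collection are unaffected.
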